#### **1.3.6.2    *Clinical Efficacy to Date***

##### ***Ipilimumab Monotherapy***

Overall survival and other efficacy endpoints were assessed in ipilimumab studies.

- OS: Ipilimumab (at 3 and 10 mg/kg) prolongs survival in subjects with advanced melanoma (previously treated with 3 mg/kg monotherapy and previously untreated with 10 mg/kg ipilimumab + DTIC)
- Best Objective Response Rate (BORR): By the conventional mWHO criteria confirmed objective responses have been observed in subjects receiving ipilimumab. These responses tend to be

durable with the median duration of responses of 11.47 months (3 mg/kg ipilimumab + gp100) and 19.3 months.

- Disease control rate (DCR): Disease stabilization in subjects receiving ipilimumab monotherapy is a key characteristic of anti-tumor activity. Durable stable disease (SD) or a slow steady decline of tumor lesion size over time has been observed. Consequently, SD, as well as objective responses, (both captured in DCR) are important for completely characterizing anti-tumor activity of ipilimumab.
- PFS: Statistically significant results in favor of ipilimumab-treated groups were observed for PFS indicating consistency of efficacy results in 2 Phase 3 trials.
- Exploratory efficacy endpoints: Four distinct response patterns have been observed following ipilimumab monotherapy.
- Shrinkage in baseline lesions, without new lesions.
- Durable SD (in some patients followed by a slow, steady decline in total tumor burden).
- Response after an increase in total tumor burden.
- Response in the presence of new lesions.

Based on these observations, subjects should receive the entire induction regimen (4 doses) as tolerated, regardless of the appearance of new lesions or growth of existing lesions during induction. Assessments of tumor response should be conducted only after completion of induction therapy and, if possible, confirmed.

In melanoma, ipilimumab prolonged survival in subjects with pre-treated and previously untreated, advanced melanoma, based on results from 2 large, multinational, double-blind, Phase 3 studies (MDX010-20 and CA184024), supported by data from key Phase 2 studies.

The Phase 3 study MDX010-20 has demonstrated a clinically meaningful and statistically significant survival benefit in pre-treated advanced melanoma. The study compared the overall survival (OS) of ipilimumab plus a melanoma-specific vaccine (gp100) to that of gp100 alone. A second comparison defined the OS of ipilimumab alone vs. gp100 alone. Both comparisons demonstrated statistically significant improvements in OS ( $p = 0.0004$  and  $0.0026$ , respectively). The 1-year survival for the two ipilimumab-containing groups, respectively, was 44% and 46% respectively, compared to 25% for the gp100 control group. The 2-year survival was 22%, 24% and 14% respectively. The median survival was

10, 10.1, and 6.4 months, for ipilimumab plus gp100, ipilimumab monotherapy, and gp100 monotherapy, respectively.

In MDX010-20, all response-related endpoints (BORR, DCR, and PFS) showed consistent, positive results for the ipilimumab-containing groups relative to the gp100 group. Response duration was longer than 2 years in 60.0% (9/15) of responders in the ipilimumab monotherapy group (range: 26.5+ to 44.2+ months) and 17.4% (4/23) of responders in the ipilimumab + gp100 group (range: 27.9+ to 44.4+ months). None of the subjects treated with gp100 remained in response at the 2-year time point. The development or maintenance of objective response or disease control following ipilimumab treatment in MDX010-20 was similar with or without the use of systemic corticosteroids.

The primary objective of CA184-024 study was the comparison of OS in subjects administered ipilimumab (10 mg/kg) + DTIC vs DTIC monotherapy. The HR for comparison of OS between the groups was 0.72 (95% CI: 0.59, 0.87; P = 0.0009), indicating a 28% risk reduction in OS for the ipilimumab + DTIC group compared with the DTIC monotherapy group. The median OS was 11.2 months (95% CI: 9.4, 13.6) in the ipilimumab + DTIC group and 9.1 months (95% CI: 7.8, 10.5) in the DTIC monotherapy group. The Kaplan-Meier survival curves are similar for the groups through approximately the first 4 months of treatment, after which a separation in the curves suggests a favorable OS advantage for the ipilimumab + DTIC group. The long-term survival effect of ipilimumab is reflected in the estimated survival rates, which were consistently higher for the ipilimumab + DTIC group relative to the DTIC monotherapy group. In the ipilimumab + DTIC group, the median duration of response (complete response/partial response [CR/PR]) using mWHO criteria was 19.3 months, and the median duration of SD was 4.7 months, as determined by the Independent Review Committee (IRC). In the DTIC monotherapy group, the median duration of response was 8.1 months and the median duration of stable disease was 4.6 months. The overall median durations of response were the same as for those subjects who received maintenance dosing.

### ***1.3.6.3 Summary of Safety***

#### ***Ipilimumab Monotherapy***

##### **Advanced Melanoma - ipilimumab 3 mg/kg**

The safety profile of ipilimumab at 3 mg/kg in the Phase 3 study MDX010-20 was consistent with that observed at 3 mg/kg in the Phase 2 studies. The most common treatment-related AEs in subjects who received ipilimumab 3 mg/kg were irAEs affecting the skin and GI tract (eg, pruritus, rash, and diarrhea).

The majority of these events were Grade 1 to 2 in severity. The most common Grade 3 to 4 treatment-related AEs were GI irAEs of colitis and diarrhea (reported in 3% to 5% of subjects).

Diarrhea and colitis were consistently among the most common treatment-related AEs during the induction phase leading to discontinuation of ipilimumab. In MDX010-20, treatment-related AEs leading to discontinuation were reported in 9.9%, 6.8%, and 3.0% of the subjects in the ipilimumab monotherapy, ipilimumab plus gp100, and gp100 monotherapy groups, respectively. The most common (> 1% of subjects in either the ipilimumab monotherapy group or ipilimumab plus gp100 groups) treatment-related AEs leading to discontinuation in the ipilimumab groups were colitis (2.3% and 2.4%), diarrhea (1.5% and 2.6%), and uveitis (1.5% and 0%). In the pooled 3 mg/kg group from the Phase 2 studies, 8.1% of subjects reported treatment related AEs leading to discontinuation, the most common were hypopituitarism (2.7%), colitis (1.8%), and decreased appetite (1.8%).

Diarrhea and colitis were consistently the most common treatment-related SAEs reported for subjects receiving ipilimumab across studies. In MDX010-20, treatment-related SAEs were reported in 16.8%, 12.6%, and 3.8% of the subjects in the ipilimumab monotherapy, ipilimumab plus gp100, and gp100 monotherapy groups, respectively. The most common (> 1% of subjects in either the ipilimumab monotherapy group or ipilimumab plus gp100 groups) treatment-related SAEs in the ipilimumab groups were colitis (5.3% and 3.4%), diarrhea (3.8% and 3.4%), hypophysitis (1.5% and 0.3%), hypopituitarism (1.5% and 0.8%), renal failure (1.5% and 0%), hypotension (1.5% and 0%), and pyrexia (0% and 1.1%). In the pooled 3 mg/kg group from the Phase 2 studies, 17.1% of subjects reported treatment related SAEs; the most common were colitis (4.5%), diarrhea (4.5%), hypopituitarism (2.7%), and pyrexia (2.7%).

Across the 3 groups in MDX010-20 and the pooled 3 mg/kg group from the Phase 2 studies, approximately 20% to 30% of subjects died during the induction phase. Most (> 90%) of the deaths were due to disease progression or other causes considered unrelated to study drug. In MDX010-20, treatment-related deaths (defined as a treatment-related AE with an outcome of death, reported at any time during the study) were reported in 4 subjects (3.1%), 8 subjects (2.1%), and 2 (1.5%) subjects in the ipilimumab monotherapy, ipilimumab plus gp100, and gp100 monotherapy groups, respectively. Of the 12 treatment-related deaths in the 2 ipilimumab-containing groups, 7 were associated with an irAE (GI perforation [4], colitis [1], liver failure [1], and Guillain-Barré Syndrome [1]). In addition, 1 subject in the ipilimumab plus gp100 group of MDX010-20 had a Grade 4 skin irAE (Stevens Johnson syndrome/toxic epidermal necrolysis/Lyell's syndrome), but died due to a treatment-related acute respiratory distress syndrome, which is not considered to be an irAE. In the pooled group from the Phase 2 studies, 2 subjects (1.8%) experienced treatment-related deaths, 1 of which was associated with an irAE (GI perforation).

## 1.4 Study Rationale

Metastatic melanoma is an aggressive tumor associated with very poor prognosis. The median survival of patients with advanced or metastatic disease is in the range of 6 months, mainly depending on location and number of metastases and patient performance status.

Until recently, medical treatment for metastatic melanoma has been highly unsuccessful with no impact on patients' survival. However, the increasing knowledge of melanoma immune-biology has prompted studies to identify new therapeutic strategies able to generate more effective host's immune responses against neoplastic cells. Among these, targeting of cytotoxic T-lymphocyte antigen-4 (CTLA-4), a key immune checkpoint molecule, by the monoclonal antibody (mAb) designated ipilimumab has emerged as the therapeutic prototype of immunomodulating mAb.

Ipilimumab is a fully human mAb (IgG1k) with high affinity for CTLA-4 molecule that blocks the binding of CTLA-4 to its receptor B7, thereby preventing down-regulation of the immune response. Ipilimumab increases the proliferation of activated T cells and potentiates the interaction between T cells and cancer cells. Ipilimumab has been approved by FDA and EMA for the treatment of metastatic melanoma since in two pivotal trials it significantly improved the survival of subjects with advanced melanoma (unresectable Stage III or Stage IV).

In spite of the limited number of objective responses (~15%) observed across a spectrum of doses and schedules of administration, in treatment-naïve and pre-treated patients, about 20% of subjects experienced a long-term survival. The latter was observed in phase II/III studies, and in the daily practice as demonstrated by two large Expanded Access Programs; noteworthy, survival rates plateaued at 3 years.

These highly encouraging results have provided the basis to identify new therapeutic strategies to further improve the clinical efficacy of ipilimumab in melanoma patients, and more broadly in subjects with solid and hematologic malignancies. Therefore, various combinations of ipilimumab with other immune-modulating, antiangiogenic, or chemotherapeutic or targeted agents are being tested, and are beginning to demonstrate the potential for synergy. In this setting, the identification of effective combination(s) of ipilimumab with novel immunomodulatory agents is particularly intriguing.

Extensive in vitro and in vivo studies focused on human melanoma, as well as several other tumor histotypes, allowed us to demonstrate a striking immunomodulatory activity of the DNA hypomethylating agent (DHA) 5-aza-2'-deoxycytidine (5-AZA-CdR), (for review see Sigalotti et al.). This bulk of experimental evidences led us to hypothesize that 5-AZA-CdR could represent a useful drug to combine with immunotherapeutic agents, including ipilimumab, to develop novel chemo-immunotherapeutic

approaches for the treatment of melanoma patients and, more broadly, of subjects with solid and hemopoietic malignancies.

Most recently, we have demonstrated that the second-generation DNA hypomethylating agent SGI-110 also holds a strong immunomodulatory activity. SGI-110 induced/up-regulated the expression of different cancer/testis antigens (CTA) (i.e., MAGE-A1, MAGE-A2, MAGE-A3, MAGE-A4, MAGE-A10, GAGE 1-2, GAGE 1-6, NY-ESO-1, and SSX 1-5) in cancer cell lines of different histotype, both at mRNA and at protein levels. Moreover, quantitative methylation-specific PCR (qMSP) analyses identified a hypomethylation of MAGE-A1 and NY-ESO-1 promoters in SGI-110-treated melanoma cells, supporting the direct role of pharmacologic DNA demethylation in CTA induction. SGI-110 also up-regulated the expression of HLA class I antigens and of the accessory molecule ICAM-1, resulting in an improved recognition of cancer cells by gp100-specific cytotoxic T lymphocytes.

Consistent with these in vitro observations, subsequent in vivo studies with human melanoma xenografts excised from SGI-110-treated mice allowed us to demonstrate a direct correlation between promoter demethylation and induction/up-regulation of the expression of different CTA in tumor tissues.

Additional data supporting the immunomodulatory activity of SGI-110 derived from the analysis of MDS or AML patients enrolled in a randomized phase 1-2 study in which the hypomethylating activity of SGI-110 on promoters of specific CTA, and the induction/up-regulation of their expression was tested. qMSP analyses showed that SGI-110 was able to reduce the constitutive methylation levels of NY-ESO-1 and MAGE-A1 promoters and to induce/up-regulate the expression of NY-ESO-1, MAGE-A1, and MAGE-A3 in treated patients.

Consistent with our previous observations with 5-AZA-CdR10, SGI-110 significantly improved the therapeutic efficacy of an anti-CTLA-4 mAb in a syngeneic murine mammary carcinoma model. The best antitumor effect was achieved in mice treated with SGI-110 followed by the anti-CTLA-4 mAb. Noteworthy, no body weight loss was observed in investigated mice suggesting for a good tolerability of the therapeutic combination.

Altogether, the evidence above provide a strong pre-clinical rationale to design novel trials combining DHA and immunotherapeutic agents; among these, the combination between DHA and anti-CTLA4 blocking mAb appears of particular interest to be explored.

#### ***1.4.1 Rationale for Combination Therapy with SGI-110 and Ipilimumab***

The trial will determine the MTD, safety and the additional benefit achieved from adding SGI-110 to ipilimumab therapy in metastatic melanoma patients. Preclinical evidence generated with SGI-110 in vivo

demonstrated that besides having a direct activity on tumor growth as a single agent, SGI-110 was able to “sensitize” neoplastic cells to the anti-tumor activity of CTLA-4 blockade, providing a sound scientific rationale to develop new immunotherapeutic approaches combining SGI-110 with therapeutic mAb to immune check-points.

## 1.5 Overall Risk/Benefit Assessment

In the clinical trials conducted to date, SGI-110 has shown antitumor activity with a manageable safety profile. The two main drug-related adverse reactions of SGI-110 are myelosuppression (neutropenia, febrile neutropenia, thrombocytopenia, and anemia) and injection-site events such as pain, irritation, and inflammation. At the SGI-110 doses and schedule proposed in this study (15-60 mg/m^2 day on Days 1-5), there have been no reports of drug-related myelosuppression in MDS and AML subjects in study SGI-110-01. The starting dose of 30 mg/m^2 day on Days 1-5 is 33% of the MTD for single-agent treatment with SGI-110. However, SGI-110 is generally administered in 28 day cycles and in this study will be administered in 21 day cycles. Despite the lack of overlapping toxicity with ipilimumab, the conservative starting dose and opportunity for de-escalation are in place for that reason.

Pain and burning at the injection site has been reported that are related to dose and volume of injection. These AE are Grade 1 and easily managed with icing of the site before and after injection. Other than these events described above, SGI-110 has been well tolerated up to 90 mg/m^2 day x5 and 125 mg/m^2 weekly x3 in 28 day cycles. For more detailed information, please refer to the IB for SGI-110.

The anti-CTLA-4 mAb ipilimumab, improves survival of metastatic melanoma with a well-known safety profile; the most common treatment-related AEs in subjects who received ipilimumab 3 mg/kg were irAEs affecting the skin and GI tract (eg, pruritus, rash, and diarrhea). Established treatment guidelines are actually available to safely manage the immune-related Adverse Events related to ipilimumab. For more detailed information, please refer to the IB for ipilimumab. The safety profile of SGI-110 in combination with ipilimumab will be tested for the first time in this trial, however due to the different nature of two compounds no overlapping toxicity will be expected. Evidences generated with SGI-110 in vivo demonstrated that besides having a direct activity on tumor growth as a single agent, SGI-110 was able to “sensitize” neoplastic cells to the anti-tumor activity of CTLA-4 blockade, improving its efficacy.

## **2 STUDY OBJECTIVES**

### **2.1 Primary Objective**

To assess Maximum Tolerated Dose (MTD) and safety of SGI-110 in combination with ipilimumab in 21 day cycles in melanoma patients.

### **2.2 Secondary Objectives**

- To evaluate the immune-related (ir) -Disease Control Rate (ir-DCR), immune-related (ir) - Objective Response Rate (ir-ORR), immune-related (ir) -Time to Response (ir-TTR) and immune-related (ir) -Duration of Response (ir-DOR)
- To evaluate median immune-related (ir) Progression Free Survival (ir-PFS), median Overall Survival (OS), and survival rate at 1 and 2-years

### **2.3 Exploratory Objectives**

- To investigate immune-biologic correlates to treatment with SGI-110 in combination with ipilimumab (see **Appendix A**)
- Characterize pharmacokinetic profile of SGI-110 and decitabine. For a detailed workplan of pharmacokinetic analyses (see **Appendix B**)

## **3 ETHICAL CONSIDERATIONS**

### **3.1 Good Clinical Practice**

This study will be conducted in accordance with Good Clinical Practice (GCP), as defined by the International Conference on Harmonization (ICH) and in accordance with the ethical principles underlying European Union Directive 2001/20/EC and the United States Code of Federal Regulations, Title 21, Part 50 (21CFR50).

The study will be conducted in compliance with the protocol. The protocol and any amendments and the subject informed consent will receive Institutional Review Board/Independent Ethics Committee (IRB/IEC) approval/favourable opinion prior to initiation of the study.

### **3.2 Institutional Review Board/Independent Ethics Committee**

Before study initiation, the investigator must have written and dated approval/favourable opinion from the IRB/IEC for the protocol, consent form, subject recruitment materials/process (e.g., advertisements), and any other written information to be provided to subjects. The investigator or sponsor should also provide the IRB/IEC with a copy of the Investigator Brochure or product labelling, information to be provided to subjects and any updates.

The investigator or sponsor should provide the IRB/IEC with reports, updates and other information (e.g., expedited safety reports, amendments, and administrative letters) according to regulatory requirements or institution procedures.

### **3.3 Informed Consent**

Investigators must ensure that subjects, or, in those situations where consent cannot be given by subjects, their legally acceptable representatives, are clearly and fully informed about the purpose, potential risks, and other critical issues regarding clinical studies in which they volunteer to participate. Freely given written informed consent must be obtained from every subject or, in those situations where consent cannot be given by subjects, their legally acceptable representative, prior to clinical study participation, including informed consent for any screening procedures conducted to establish subject eligibility for the study. The rights, safety, and well-being of the study subjects are the most important considerations and should prevail over interests of science and society.

Appendix 1 contains Fondazione NIBIT/CRO procedures on obtaining informed consent from subjects, or, in those situations where consent cannot be given by subjects, their legally acceptable representative prior to participating in a clinical study. Procedures are described for all subjects, including those who are unable to give informed consent. The relevant procedures must be used whenever they are applicable (see subject selection criteria in Sections 4.2.1 and 4.2.2)

## **4 INVESTIGATIONAL PLAN**

### **4.1 Study Design and Duration**

This is a phase Ib, dose-escalation study aims to evaluate the safety, tolerability, and Maximum Tolerated Dose (MTD) of SGI-110 in combination with ipilimumab a 21 day cycle in melanoma patients

### 4.1.1 Study Phases

This study is divided into 3 phases: the Screening Phase, the Treatment Phase, and the Follow-up Phase. After informed consent is obtained, patients will enter the Screening Phase to assess eligibility criteria. Upon meeting criteria, eligible patients will receive either the combination of SGI-110 and ipilimumab.

Eligible subjects will enter a Treatment Phase within 3 days to receive:

SGI-110: starts at 30 mg/m^2 day s.c. on W0, 3, 6, 9 Day 1 - 5 q21 days. Dose Level -1: 15 mg/m^2 day; Dose Level +1: 45 mg/m^2 day, Dose Level +2: 60 mg/m^2 day and ipilimumab: 3 mg/Kg i.v. over 90 minutes on W1, 4, 7 and 10 for a total of 4 cycles.

[figure not shown]

Figure 1

The dose escalation of SGI-110 will follow a traditional 3+3 design: Cohorts of 3-6 patients will receive a combination therapy of SGI-110 and Ipilimumab 3mg/kg. Dose escalation will be dependent on the available toxicity information (including adverse events that are not DLTs), PK, and PD information, as well as the recommendations from the scientific committee. During the dose escalation, subjects will be allocated to 1 of 4 dose levels of SGI-110 in combination with the standard schedule of ipilimumab (see Figure 1). Treatment within the 4 SGI-110 dose levels will proceed in sequence based upon the incidence of DLTs (see Section 5.2.2). Details of this evaluation and the thresholds for toxicity and dose escalation are described fully in Section 5.3. The total number of subjects enrolled will depend on the observed DLTs, and is expected to be up to 19 subjects.

Study Phases are further detailed below:

#### Screening Phase

- Begins after the patient signs the Informed Consent Form;
- Ends before Treatment Phase;
- Establishes patient eligibility;

- Provides characteristics, including the baseline disease status for the response assessment.
- After informed consent has been obtained, the subject must be enrolled into the study by registration on the eClinical platform to obtain the subject number (STEP1).

### ***Treatment Phase***

Following completion of all Screening Phase evaluation, and checking inclusion criteria site personnel will make patient registration to obtain a treatment assignment (STEP2). The e-Clinical system assigns subjects to the SGI-110 dose level.

### ***Follow-up Phase***

Begins for the patients when they:

- Withdraw consent from study procedures but not from Follow-up;
- Experience irPD.
- 30 days after final treatment dosing;
- No TAs for patient that experienced irPD;
- Telephone contact every 12 weeks to evaluate overall survival (OS), and inquire about AE resolution, if applicable and subsequent anti-cancer treatments.

Refer to the Flow Chart/Time and Events Schedule in Section 6.0 and Sections 6.3 for a complete and detailed list of all procedures associated with the study phases.

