### ***4.1.2 Tumor Assessments (TA)***

Tumor assessment with radiographic imaging (e.g. MRI-CT of brain, CT of chest, abdomen, pelvis, other soft tissues) and digital photographs of skin lesions will be performed for all subjects at Screening, week 12, then every 6 weeks at weeks 18, 24, and every 12 weeks from week 24 onwards, for all non-progressing subjects. At each evaluation investigators will assess the overall response (complete response (CR), partial response (PR), stable disease (SD) or Progressive Disease (PD) (as categorized by irRC).

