#### ***4.1.2.1 Confirmed ir-Disease Progression***

Unless they are rapidly deteriorating, those patients who experience ir-disease progression, as determined by the investigator, should have confirmation of irPD at the next scheduled TA (see Tab.6.1). Increases in lesion size detected radiologically or upon gross examination could be misinterpreted as progressive tumor growth since ipilimumab can produce an influx or expansion of tumor infiltrating lymphocytes. Therefore no subsequent anti-cancer treatment should be given prior to confirmed irPD. See Section 6.4.

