#### ***4.1.2.2 Tumor Assessment Schedule Rationale***

Ipilimumab is expected to trigger immune-mediated responses, which require activation of the immune system prior to the observation of clinical responses. Such immune activation may take weeks to months. Some patients with advanced melanoma may have objective volume increase of tumor lesions within 12 weeks after inclusion in the study. Such patients may have not had sufficient time to develop the required immune activation or, in some patients, tumor volume increases may represent infiltration of lymphocytes into the original tumor. In conventional studies, such tumor volume increases during the first 12 weeks of the study would constitute PD and lead to discontinuation of imaging to detect response, thus disregarding the potential for subsequent immune-mediated clinical response. Therefore, in this study, patients with tumor volume increase detected at Week 12 but without rapid clinical deterioration will continue to be clinically observed with a stringent imaging schedule to allow detection of a subsequent tumor response. This will improve the overall assessment of the clinical activity of ipilimumab and more likely capture its true potential to induce clinical responses. Tumor assessments will be made using the immune-related (ir) tumor response criteria. See Sections 6.4.3.5.

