| Ipilimumab Infusion      |                         |            | X                                                |            |            | X          |            | X          |            | X           |                        |             |             |               |                         |                         |
|                                 |                         |            |                                                  |            |            |            |            |            |            |             |                        |             |             |               |                         |                         |
|                                 |                         |            |                                                  |            |            |            |            |            |            |             |                        |             |             |               |                         |                         |

- If Screening physical is conducted within 24 hours of study drug dosing then a single physical may count as both the Screening and Week 1 examination. Additional Physical Examinations should be performed as clinically indicated. Vital signs to be performed as described in Section 6.3.2.
- The visits will occur on every treatment day and also on Day 8, for all cycles, on Day 8,15 for the first cycle. There is a 30-day (+ 5 day) safety visit after the last study treatment in this study.
- Urine analysis to be performed at Screening and then as clinically indicated during the study.
- CT Scans with IV contrast and oral contrast of neck, chest, abdomen, pelvis, and  $\pm$  soft tissue (or MRI, if iodine contrast media is medically contra-indicated) have to be acquired for ALL patients at all TA timepoints. TA will be performed for all subjects at Screening and 12, then every 8 weeks at Week 20, 28, 36, then every 12 weeks from Week 36 onwards for all non-progressing patients.
- Patients who discontinue dosing when being progression free will be followed with Tumor Assessments until PD, unless patient withdraws consent.

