***Definition of Overall Response Using irRC Will Be Based on the Following Criteria:***

- Immune-related Complete Response (irCR): Complete disappearance of all tumor lesions (index and non-index together with no new measurable/unmeasurable lesions) for at least 4 weeks from the date of documentation of irCR.
- Immune-related Partial Response (irPR): The sum of the products of the 2 largest perpendicular diameters of all index lesions is measured and captured as the SPD baseline. At each subsequent TA, the sum of the products of the 2 largest perpendicular diameters of all index lesions and of new measurable lesions are added together to provide the Immune Response Sum of the Product of the Diameters (irSPD). A decrease, relative to baseline of the irSPD of 50% or greater is considered an irPR. It must be confirmed no less than 4 weeks from the first irPR.
- Immune-related Stable Disease (irSD): irSD is defined as the failure to meet criteria for immune complete response or immune partial response, in the absence of progressive disease.
- Immune-related Progressive Disease (irPD): Unless the subject is rapidly deteriorating, a confirmatory scan not less than 4 weeks since the prior scan should be performed to confirm PD. Any of the following will constitute progressive disease:
  - At least 25% increase in the SPD of all index lesions over nadir SPD calculated for these lesions.
  - At least a 25% increase in the SPD of all index lesions and new measurable lesions (irSPD) over the nadir SPD calculated for the index lesions.

Immune-related clinical activity (irCR, irPR or irSD) relative to baseline can be recorded at any time, including after confirmed irPD, provided that the patient has not received alternative non-ipilimumab anticancer therapy.

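### The Follow-up rule that ends tumour assessments at irPD contradicts the confirmation and late-response rules, and Table 6.1 carries two scan calendars; both affect secondary efficacy endpoints only

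*Combined protocol and SAP*

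**What the plan says.** **When assessments end.** In section 4.1.1, the Follow-up Phase begins for patients who experience irPD, among other triggers. It then states "No TAs for patient that experienced irPD" and provides telephone contact every 12 weeks. The word confirmed does not appear.

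Other sections say:

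- Section 4.1.2.1: patients with irPD, unless rapidly deteriorating, "should have confirmation of irPD at the next scheduled TA", with a pointer to Table 6.1.
- Section 4.1.2.2: patients with growth at Week 12 but no rapid deterioration "will continue to be clinically observed with a stringent imaging schedule to allow detection of a subsequent tumor response".
- Section 6.4.3.3, overall-response definition: "a confirmatory scan not less than 4 weeks since the prior scan should be performed to confirm PD", again unless rapidly deteriorating. It adds that irCR, irPR or irSD "can be recorded at any time, including after confirmed irPD", provided no alternative anticancer therapy has been given.
- Synopsis, Duration of Study: efficacy follow-up runs to confirmed PD. Section 4.1.6 and the last footnote to Table 6.1 say PD only.

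**Scan calendar.** Section 4.1.2 has Week 12, "then every 6 weeks at weeks 18, 24, and every 12 weeks from week 24 onwards". The synopsis and the Table 6.1 columns agree with it. A footnote to the same table has Week 12, "then every 8 weeks at Week 20, 28, 36, then every 12 weeks from Week 36 onwards".

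**Endpoints.** irORR and irDCR (8.3.2.1) are built on irBOR, which uses all available assessments before subsequent therapy (6.4.3.4). irPFS (8.3.2.2) ends at progression per irRC or death, and irDoR (8.3.2.1) at irPD or death. Neither says whether the date is that of first or confirmed irPD.

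**The concern.** irRC is used here because responses may come late or follow apparent growth. Section 1.3.6.2 lists response after an increase in tumour burden among the observed patterns. The End of Treatment text puts median time to response for both agents above 100 days, whereas the first on-study scan is at Week 12, which is 12 × 7 = 84 days. A rule that ends scheduled scans at an irPD not yet confirmed works against that purpose. A delayed responder would stay classed as progressing, so irORR and irDCR could be biased downward, and an apparent progression could stand as an irPFS event without the scan that would confirm or overturn it. Scans never taken cannot be recovered at analysis.

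The calendar conflict is a different problem. It concerns when a progression or response is first seen, and so the dates that enter irPFS, irTTR and irDoR.

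**Working it through.** The protocol states that no formal sample size calculation was done, so there is no planned figure to reproduce. The check is a comparison of texts plus some illustrative arithmetic.

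**1. The stop rule under each reading**

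| Reading of the Follow-up text | Confirmation (4.1.2.1, 6.4.3.3) | Imaging after Week 12 growth (4.1.2.2) | Credit after confirmed irPD (6.4.3.3) |
|---|---|---|---|
| Any irPD | Conflict | Conflict where the growth meets irPD | Conflict |
| Confirmed irPD only | Compatible | Compatible until confirmation | Conflict: credit allowed, no scheduled scan to supply it |

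No reading removes every conflict.

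**2. Size of one reclassification** (assumed; the documents give no rate of response after irPD)

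- Maximum N is 19: 1/19 = 5.3 points. Minimum N is 6: 1/6 = 16.7 points.
- Section 1.4 cites about 15% objective responses to ipilimumab, roughly 3 of 19. With the exact binomial intervals of section 8.4.3:
  - 3/19 = 15.8% (95% CI 3.4 to 39.6)
  - 2/19 = 10.5% (95% CI 1.3 to 33.1)
- If a proportion q of patients respond or stabilise after a first irPD, the chance that at least one of 19 is affected is 1 − (1 − q)^19. For assumed q of 2%, 5% and 10% this is 32%, 62% and 86%.

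**3. The two calendars**

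A (synopsis, 4.1.2, table columns): Weeks 12, 18, 24, 36, then every 12 weeks. B (footnote): Weeks 12, 20, 28, 36, then every 12 weeks. The detected date is the first scan on or after the true progression.

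| True progression (weeks) | Detected under A | Detected under B | B − A |
|---|---|---|---|
| 12–18 | 18 | 20 | +2 |
| 18–20 | 24 | 20 | −4 |
| 20–24 | 24 | 28 | +4 |
| 24–28 | 36 | 28 | −8 |
| 28–36 | 36 | 36 | 0 |

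If progression is uniform over Weeks 12 to 36 (an assumption):

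- mean absolute shift = (6×2 + 2×4 + 4×4 + 4×8 + 8×0)/24 = 68/24 = 2.8 weeks
- mean signed shift = (12 − 8 + 16 − 32)/24 = −0.5 week

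An irPD at Week 12 would be confirmed at Week 18 (A) or Week 20 (B), an interval of 6 or 8 weeks. Both exceed the 4-week minimum. Each calendar has two scans between Weeks 12 and 36, so the number of chances to record a response is the same.

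**The case against.** The strongest reply is that the Follow-up text means confirmed irPD. It does not say first irPD, the synopsis follows patients to confirmed PD, and section 4.1.2.1 is devoted to confirmation. This partly stands: a reader might infer that the protocol plainly stops scanning at the first irPD, and the text is not that explicit. But section 4.1.2.1 itself speaks of patients experiencing progression that is not yet confirmed, section 4.1.6 and the table footnote say PD alone, and even the favourable reading conflicts with the credit after confirmed irPD.

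A reader might also infer that confirmation and late response could never be observed. That goes too far. Section 6.4.3.2 allows extra assessments on suspicion of progression, irBOR counts every available assessment, and the late-credit clause permits recording without ordering a scan. What is lost is the scheduled scan.

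On the calendar, the table has no Week 20 or Week 28 column and there is one centre, so the footnote may be a leftover. The documents do not show that patients would in fact be scanned on different calendars. The contradiction still stands, because section 4.1.2.1 sends the reader to Table 6.1 for the next scheduled assessment and that table holds both calendars.

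Finally, the secondary efficacy endpoints are exploratory (8.4.3) and both illustrative intervals are wide, so one patient hardly changes inference. This limits severity but does not remove the contradiction.

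**Conclusion.** Two separate internal contradictions stand, and both should be fixed.

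- **Stop rule.** Taken literally, it can bias irORR and irDCR downward and leaves the irPFS event ambiguous. Each affected patient is worth 5.3 points at N = 19. How many would be affected is unknown, because the documents give no delayed-response rate.
- **Calendar.** It moves detected dates for irPFS, irTTR and irDoR by 0 to 8 weeks. The 8 weeks arises only for progression in Weeks 24 to 28; the mean absolute shift is about 2.8 weeks under the uniform assumption. It would be wrong to infer a material effect on irORR or irDCR, since both calendars offer the same number of scans and both allow the 4-week confirmation.

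Neither contradiction touches the primary endpoint of MTD and safety. The one link to study conduct is the synopsis option to terminate if no immune-related disease control is seen. That is discretionary and concerns a count of zero, so it does not raise the point above a correction to exploratory secondary endpoints.

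**What to change.** 1. Reconcile the Follow-up Phase text in 4.1.1, section 4.1.6 and the Table 6.1 footnote with the synopsis (Duration of Study), 4.1.2.1, 4.1.2.2 and the overall-response definition in 6.4.3.3. State once whether assessments end at unconfirmed or confirmed irPD, in a form compatible with the confirmatory scan already called for.
2. In 6.4.3.3, either state which assessments inform the clause on activity after confirmed irPD, or remove that clause.
3. In 8.3.2.1 and 8.3.2.2, state whether irDoR and irPFS are dated at first or confirmed irPD. Correcting the Follow-up text alone would leave this open.
4. Reconcile the Table 6.1 footnote with the table's columns, the synopsis and 4.1.2, so that one scan calendar remains.

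The cost is wording, plus the confirmatory scan that 4.1.2.1 and 6.4.3.3 already call for. Any scans kept after confirmed irPD would be additional imaging and should be named as such.
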